## **6. PROTOCOL DESIGN**

### **6.1 Overall Study Design**

Thirty patients (males and females) ages 20 to 65 who, at Screening, meet ICD-10 criteria for recurrent MDD with a current depressive episode of at least a 30-day duration, an on-site Screening MADRS score  $\geq 22$  (consistent with moderate or greater depressive symptom severity),  $\leq 30\%$  symptom decrease from web-screen, and who meet all other inclusion/exclusion criteria at Baseline will be enrolled into the study and randomized with a 1-to-1 allocation under double-blind conditions to receive a single 25 mg oral dose of psilocybin or a single 100 mg oral dose of niacin. Expecting a maximum of 20% drop out rate a maximum of 6 more subjects may be randomized, in order to reach 30 patients completed (performed all study related activities up until and including PET#2 day 15). Niacin will serve as an active placebo that provides an acute physiological response (flushing) that may aid in blinding of intervention allocation. All randomized participants will be included in the Full Analysis Set (FAS) that will be used for analyzing primary and secondary study endpoints.

Eligible participants at Screening will undergo pre dosing data acquisition, preparation session and be eligible for randomization on Dosing Day to receive either psilocybin or niacin active-placebo and will complete follow-up visits and assessments on study Day 1, 8, 15 and 42 (within corresponding visit windows). Study outcome measures will assess depressive symptoms, clinical global functioning, anxiety symptoms and health-related

quality of life. Safety outcome measures will be collected at all assessment time points from the time of consent through the end of study.

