## 16. STATISTICAL ANALYSIS

### 16.1 Power Analysis and Sample Size Determination

The difference between psilocybin and placebo in change from baseline to Day 8 in MADRS total score (primary endpoint) will be analyzed for the Full Analysis Set using Analysis of Covariance including treatment as main effect and baseline as covariate.

Based on prior controlled studies of psilocybin in cancer- related depression and anxiety, a decrease in depression symptoms from baseline to one-week post-dose of at least 30% is expected in the placebo arm. In an open-label study of psilocybin the change in MADRS total score from baseline to 1 week was -23.3. Several clinical studies in the literature report a standard deviation in change in MADRS total score around 10.

A sample size of 15 in each group will have 80% power to detect a difference in means of 11 (the difference between a psilocybin mean,  $\mu_1$ , of -23 and a placebo mean,  $\mu_2$ , of -12) assuming that the common standard deviation is 10 using a two group t-test with a 5% two-sided significance level.

Considering the short duration between treatment and primary endpoint measurement day 8 the risk of withdrawal is considered low. The total sample size is set to 30 patients completing day 15. In case of withdrawals before day 15 additional patients may be randomized to ensure 30 patients included in the primary and secondary analyses. Estimating a maximum of 20% withdrawals, a maximum of 6 additional subjects can be included.

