#### 16.4.1 Efficacy Analyses

The difference between psilocybin and placebo in change from baseline to Day 8 in MADRS total score (primary endpoint) will be analyzed for the Full Analysis Set using Analysis of Covariance including treatment as main effect and baseline as covariate. The same method will be applied for all other single measure endpoints. Treatment differences of multiple measurement endpoints will be analyzed by the mixed model repeated measurements analysis (MMRM) method.

Response and remission rate will be analyzed using logistic regression with the baseline measure as a covariate. The adjusted percentage with 95% CI, Odds Ratio with 95% CI and nominal p-values for the treatment comparison will be presented.

Time to initiation of antidepressant will be defined as the time (in days) from day 43 to the date when any antidepressant has been prescribed. Kaplan-Meier plots of time to initiation of antidepressant will be displayed by treatment groups. Time to initiation of antidepressant will be censored at study discontinuation or completion.

If the assumption of normality does not hold for a particular endpoint on the original scale of measurement, nonparametric methods (e.g. Mann Whitney U test, Fisher's exact) or common transformations (e.g., ln, sqrt) of the original data may be used.

P-values less than 0.05 will be considered statistically significant. As default all tests will be two-sided and two-sided 95% confidence intervals will be computed for the treatment difference. However, any hypothesis that includes a direction of change, eg *increased* [11C]UCB-J binding after dosing, will be tested using one-sided test using a significance level of 0.025.

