## 5. Statistical analysis

### 5.1. Power analysis and Sample Size Determination

The difference between psilocybin and placebo in change from baseline to Day 8 in MADRS total score (primary endpoint) will be analyzed for the Full Analysis Set using Analysis of Covariance including treatment as main effect and baseline as covariate.

Based on prior controlled studies of psilocybin in cancer- related depression and anxiety, a decrease in depression symptoms from baseline to one-week post-dose of at least 30% is expected in the placebo

arm. In an open-label study of psilocybin the change in MADRS total score from baseline to 1 week was -23.3. Several clinical studies in the literature report a standard deviation in change in MADRS total score around 10.

A sample size of 15 in each group will have 80% power to detect a difference in means of 11 (the difference between a psilocybin mean, of -23 and a placebo mean, of -12) assuming that the common standard deviation is 10 using a two group t-test with a 5% two sided significance level.

Considering the short duration between treatment and primary endpoint measurement day 8 the risk of withdrawal is considered low. The total sample size is set to 30 patients completing day 15. In case of withdrawals before day 15 additional patients may be randomized to ensure 30 patients included in the primary and secondary analyses. Estimating a maximum of 20% withdrawals, a maximum of 6 additional subjects can be included.

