## 5.5. Sensitivity analysis

The secondary endpoints evaluating changes in (MADRS, MADR-S, SDS, and CGI) score during different/several time points will be conducted by using MMRM models, fitting treatment, timepoint, and a treatment\*timepoint interaction. The models will be built as of the primary endpoint (see 5.4 Primary analysis). Paired t-test will be performed for between-groups comparisons at all time points, and between all time points over time against baseline. Response will be defined as  $\geq 50\%$  decrease (MADRS and MADR-S) compared to the last measurement before dosing, and remission will be defined as a (MADRS and MADR-S) score  $\leq 10$ . In addition, response will also be defined as  $> 10$  points decrease (MADRS and MADR-S) compared to the last measurement before dosing. Response and remission rate at all time points post dose will be analyzed by using Fisher's exact test and univariable logistic regression with odds ratios (OR) and their 95% confidence intervals (CI) and nominal p-values. An additional secondary endpoint will be time to initiation of antidepressant treatment. Time to initiation of antidepressant will be defined as the time (in days) from day 43 to the date when any antidepressant has been prescribed. Subjects will be censored at study discontinuation or completion. The Kaplan-Meier approach will be assessed with the log-rank test.

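### SAP 5.5 drops the baseline covariate that protocol 16.4.1 requires for response and remission, and names two unadjusted tests without saying which governs

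*Protocol*

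**What the plan says.** Protocol 16.4.1 fixes the model: "Response and remission rate will be analyzed using logistic regression with the baseline measure as a covariate". It also fixes the output: "The adjusted percentage with 95% CI, Odds Ratio with 95% CI and nominal p-values for the treatment comparison will be presented". Fisher's test appears in that section only as an example of a fallback when normality fails, where "nonparametric methods (e.g. Mann Whitney U test, Fisher's exact) or common transformations (e.g., ln, sqrt) of the original data may be used".

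SAP 5.5 fixes a different analysis for the same endpoints: "Response and remission rate at all time points post dose will be analyzed by using Fisher's exact test and univariable logistic regression". It asks for odds ratios, 95% confidence intervals and nominal p-values. It names no covariate and no adjusted percentage, and gives the two methods no order of precedence. Remission is a score of 10 or less. Response is a fall of at least 50% from the last pre-dose score, and the SAP adds a second definition, a fall of more than 10 points.

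**The concern.** The two sections cannot both be followed: a univariable model has no room for the covariate that the protocol requires. Protocol 16.4.1 does not leave this choice to the SAP, and the SAP gives no reason for the change.

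Three things follow.

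- **Lost information.** Remission is an absolute cut-off, while entry requires only a screening MADRS of at least 22, with no stated upper limit. Baseline is therefore prognostic for remission, and a chance imbalance between two arms of 15 goes uncorrected.
- **A different quantity.** The odds ratio from a baseline-adjusted model is conditional on baseline; the one from a univariable model is marginal. The SAP would not report what the protocol promises.
- **A choice of result.** Each endpoint yields two p-values. For MADRS alone, three outcomes at the five post-dose visits listed in protocol 5.5.1 (Days 8, 15, 42, 180, 365) with two tests give 3 × 5 × 2 = 30.

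**Working it through.** **The plan's own figure.** Protocol 16.1: "A sample size of 15 in each group will have 80% power to detect a difference in means of 11", "assuming that the common standard deviation is 10 using a two group t-test with a 5% two-sided significance level". The standardised difference is 11/10 = 1.1. With 15 per arm the noncentrality is 1.1 × √(15/2) = 3.012 on 28 degrees of freedom, critical value 2.048, and power is 82.8%. With 14 per arm it is 79.99%. So 15 is the smallest number reaching 80%, and the plan's figure reproduces. It concerns the primary endpoint; the documents state no power for response or remission.

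**Why baseline matters for remission.** Take the plan's means ("the difference between a psilocybin mean, of -23 and a placebo mean, of -12") and SD 10, and assume that change does not depend on baseline. A patient entering at 24 needs a change of -14 or lower; one entering at 40 needs -30 or lower.

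| Baseline | Psilocybin | Placebo |
|---|---|---|
| 24 | Φ((-14+23)/10) = Φ(0.9) = 82% | Φ((-14+12)/10) = Φ(-0.2) = 42% |
| 40 | Φ((-30+23)/10) = Φ(-0.7) = 24% | Φ((-30+12)/10) = Φ(-1.8) = 4% |

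**How the SAP's two tests can disagree.** Take 9/15 against 3/15 remitters, an illustrative table.

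- Fisher: the upper tail is (2,277,275 + 315,315 + 20,475 + 455)/86,493,225 = 0.0302, so two-sided p = 0.060.
- Univariable logistic, Wald: ln(9×12/(6×3)) = ln 6 = 1.792; SE = √(1/9 + 1/6 + 1/3 + 1/12) = 0.833; z = 2.15; p = 0.032.

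**Simulation model.** 15 per arm, allocated 1:1. Change = arm mean + slope × (baseline - mean baseline) + error, with error SD √(100 - (slope × baseline SD)²) so that the total SD stays near 10. Baseline is at least 22, and Day 8 is baseline plus change. Assumed, because the documents do not give them: baseline mean 28-40, baseline SD 4 or 6, slope 0 or -0.5. The Firth runs used means 30 and 34 only.

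**Value of the covariate alone** (adjusted against univariable, same type of test):

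| Test | Day 8 remission | 50% response |
|---|---|---|
| Likelihood ratio, unpenalised | about 2-9 points | about 1-7 points |
| Wald | about 1-7 points | about -1 to 3 points |
| Firth | about 0-8 points | about 0-3 points |

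The unpenalised adjusted likelihood-ratio test rejected in 6.5-8.3% of null remission trials, so its gains are partly excess type I error. For response I rely on the Firth and Wald rows.

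**Adjusted logistic against Fisher, Day 8 remission:**

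| Adjusted test | Gain over Fisher | Null rejection |
|---|---|---|
| Likelihood ratio, unpenalised | 18-27 points (means 28-36), up to about 31 at mean 40 | 6.5-8.3% |
| Wald | 8-18 points (means 28-34); about zero or negative at means 36-40 | 0.7-4.4% |
| Firth | 14-22 points (means 30 and 34) | about 2-5% |

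Fisher's own null rejection was about 0-2%. In one set of Firth runs, power was 52-64% for the adjusted Firth fit and 33-48% for Fisher.

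**Disagreement at 0.05** between Fisher and a univariable logistic test, Day 8 remission: 14-29% of trials with Wald or likelihood-ratio tests over all baseline scenarios, and 11-16% with a univariable Firth fit.

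**The case against.** The strongest defence has four parts.

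1. **Low stakes.** These are secondary endpoints with nominal p-values and no multiplicity adjustment, and SAP 5.2 has results read as exploratory. No decision rule hangs on 0.05. This stands and limits the weight of the point. It does not remove the contradiction, and with no multiplicity control there is more reason to name one main result in advance.
2. **A one-term model is defensible with sparse data.** The rarer outcome category had a median of about 9-13 patients at Day 8 under the planned effect, and an unadjusted odds ratio is a valid estimand. This stands in part. The covariate does need a penalised fit, and Firth-adjusted power ranged from 4-5 points below to 6 points above an unpenalised univariable likelihood-ratio test. But that univariable test rejected in 6-8% of null trials in the same runs.
3. **Response is already relative to the pre-dose score.** This stands: the power gain there is close to nothing. The case for adjusting response is consistency with the protocol.
4. **SAP 5.6 allows logistic models with predictors.** It does, but only as exploratory work. The heading of SAP 5.5 might also suggest that its tests supplement the protocol's model, yet no other SAP section analyses response or remission.

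A reader might infer that dropping the covariate costs 18-26 points of power for remission. The documents do not support that. A gap of that size appears when Fisher's test is set against an unpenalised adjusted likelihood-ratio test that rejects too often under the null. The SAP also keeps logistic regression beside Fisher's test, so Fisher alone is not the right comparator for the covariate.

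**Conclusion.** The contradiction is certain: protocol 16.4.1 and SAP 5.5 specify different analyses for the same endpoints, and the SAP leaves two results without precedence.

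The size is moderate and conditional. The covariate is worth roughly 0-9 points of power for Day 8 remission and about 0-3 for 50% response. The larger gap for remission, about 14-22 points between a baseline-adjusted Firth fit and Fisher's test, mostly reflects Fisher's conservatism. The SAP's two tests disagree at 0.05 in roughly 11-29% of simulated trials, depending on the scenario and the logistic test used. All these figures use the plan's changes and SD with an assumed baseline mean, SD and slope, so they should be read as ranges. The change should be made, but it touches secondary endpoints only and leaves the primary conclusion as it is.

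**What to change.** Reconcile protocol 16.4.1 and SAP 5.5 by naming one main analysis in SAP 5.5:

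- logistic regression of response and of remission on treatment, with the baseline score of the same scale (MADRS or MADRS-S) as covariate;
- a Firth penalty, because events are few and some visits may have empty cells;
- adjusted percentages, odds ratio and 95% CI reported, as the protocol promises;
- Fisher's exact test kept only as a labelled supportive analysis.

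The cost is SAP wording and one model term. The baseline scores are already collected. The small downside is having to specify and run a penalised fit.

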## 5.6. Exploratory analysis

The Exploratory analysis will be descriptive between-group differences to support the primary and the secondary analysis as described in section 5.3. In addition, independent predictors will be evaluated using linear (continuous outcome), mixed-linear (repeated outcome), logistic (binary outcome) or Cox (time to event outcome) regression models based on the nature of the data.

## 5.7. Safety analysis

The number and percentage of subjects experiencing one or more treatment-emergent AEs in the following categories will be summarized. No statistical testing will be performed on the safety data.

- Incidence of AEs by severity
- Incidence of AEs leading to termination from the study
- Incidence of TEAEs
- Incidence of TEAEs by severity
- Incidence of SAEs
